## Methods – design

We propose to carry out an observational non-randomized prospective clinical trial on patients diagnosed with an early SSCC where 3 subgroups are studied in parallel:Arm 1: Radiotherapy ± chemotherapy (RCT)Arm 2: Trans-oral Laser Microsurgery (TLM)Arm 3: Trans-Oral Robotic Surgery (TORS)

The inclusion will be multicentric and international. The treatment will be chosen by the local multidisciplinary tumor board (MTB) according to the primary cTNM-stage, the patient preferences and the local standard of care based on peer-reviewed international guidelines (Fig. 1, SPIRIT Flow Chart and Fig. 2, Trial Design). The guidelines to be followed are the National Comprehensive Cancer Network (NCCN) [31] or the European guidelines including the European Head and Neck Society (EHNS), the European Society of Medical Oncology (ESMO) and the European Society for RadioTherapy and Oncology (ESTRO) [32].

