#### Arm 2 and 3: Trans-oral Surgeries

Trans-oral surgeries can be performed by TLM or by TORS. The choice of the technique will be made during the local MTB and depending the local expertise.

Surgery must be performed within the 4 weeks after pathological confirmation of SSCC with primary tumor biopsy.

A good surgical field exposure is mandatory. The use of an appropriate mouth gag is recommended. The exposure will be evaluated before the main surgery during a rigid panendoscopy. In case of doubt, the mouth gag needs to be tested during this procedure.1/ Trans-oral laser microsurgery (TLM).

A microscope with a CO_2_ laser will be used for the resection and hemostasis.

The best adapted laryngoscope to the patient anatomy should be used for an adequate exposition.

The hemostasis can be performed by a monopolar of the use of clips.

During the procedure, the superior laryngeal arteries should be ligated or clipped.2/ Trans-oral robotic surgery (TORS).

TORS will be carried out using the Da Vinci Surgical robot (Intuitive Surgical, CA, USA). Surgeons on the main console and at the bedside should have adequate training and an experience of minimum 20 cases. The spatula cautery will be used to remove the tumor and perform hemostasis at the same time. The hemostasis and bleeding prevention should be made with the bipolar or using clips. During the procedure, the superior laryngeal arteries should be ligated or clipped.3/ Handling of Surgical Margins.

The surgeon should try to achieve a minimum of 1 cm gross visual margins with > 3 mm microscopic margins. The resection needs to completely remove the tumor and *en-bloc* resection is preferred. The resection will be performed according the European Laryngological Society classification of endoscopic supraglottic laryngectomy [53]. In the TLM, the piecemeal resection is sometimes necessary to obtain adequate deep section margins. In this case, all the pieces of the specimen must be oriented and pinned carefully on the cork-board. The help of a schematic anatomical view is mandatory.

During the surgery, circumferential margins will be evaluated by frozen section peroperative analysis. These margins will be oriented as followed: superior, inferior, lateral, medial and deep. If needed, further resections will be performed until negative margins are obtain. The resected specimen should be oriented with the help of a schematic view on the cork-board.

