## Statistical analysis

The primary outcome is the total MDADI scores at 12 months between the 3 arms. Assuming that the MDADI total score is normally distributed with a standard deviation of 12 points and considering a minimal clinical difference of 10 points [63], a sample size of 30 patients per arm with a confidence of 95% and a power of 90% is sufficient to detect a clinically significant difference [64–66]. Assuming a 20% of patient’s dropout, we need to recruit 36 patients per arm (total 108).

*The baseline characteristics* of the patients in the 3 arms will be described, including demographics and tumors measures at imaging, using descriptive statistics.

Differences will be assessed with a Tukey Test for K means or similar, and Chi-square tests for counts and frequencies as required.

Any difference in patient baseline heterogeneity between the arms will be assessed by the Charlson Comorbidity Index.

If a mismatch between the 3 groups in the baseline variables is discovered; a multivariate propensity scores analysis (PSA) will be undertaken to establish conditional randomness and comparability [67, 68].

*Survival rates* will be calculated from the date of MTB until the last available follow-up date or study cut-off at 2 years using the Kaplan–Meier method with differences compared using the log-rank test.

A Cox multivariate regression analysis will be used to determine baseline factors predictive of survival.

*MDADI, QLQ-C30 and H&N43 subscales* and single-item sub-scores will be summarized by means (standard deviation) and median for each trial arm and presented graphically using boxplots by trial arm and time period. The scores of the different scales will be compared between the 3 arms using mixed models for repeated measures.

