### Why not using randomization?

First, in these small selected tumors group, patient cancer stage and tumor characteristics should be comparable (see inclusion criteria) but the influence of patient preferences is as important as the particular expertise of the individual treating medical team. Ignoring patient preferences can lead to recruitment problems, as shown in a recent study [27].

Second, the final treatment depends on the MTB decision based on the NCCN and European guidelines [31, 32] as well as the patient preference. In addition, before trial inclusion, a questionnaire will be filled in to highlight if a specific criterion has influenced the final treatment choice. We also chose to perform an observational trial to be as much possible close to real life practice (and avoiding cost linked to the randomization).

Finally, to minimize a potential center effect, patient’s inclusion is restricted to hospitals with an expertise in at least 2 different treatments modalities and treating minimum 50 cases/year. Moreover, a fixed center effect will be integrated in the statistical analysis.

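### Patient-level adjustment for confounding in a non-randomised comparison is made conditional on a baseline mismatch being found; it should be unconditional

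*Protocol article*

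**What the plan says.** The Methods – design section describes an "observational non-randomized prospective clinical trial on patients diagnosed with an early SSCC where 3 subgroups are studied in parallel". The tumour board assigns treatment "according to the primary cTNM-stage, the patient preferences and the local standard of care". For the two surgical arms, the section on trans-oral surgeries adds: "The choice of the technique will be made during the local MTB and depending the local expertise".

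The Statistical analysis section gives the endpoint: "The primary outcome is the total MDADI scores at 12 months between the 3 arms". Baseline variables, including demographics and tumour measures, are compared by Tukey and chi-square tests. It then says: "Any difference in patient baseline heterogeneity between the arms will be assessed by the Charlson Comorbidity Index". The propensity step follows: "If a mismatch between the 3 groups in the baseline variables is discovered; a multivariate propensity scores analysis (PSA) will be undertaken". No threshold for a mismatch is given. The scores are compared by mixed models for repeated measures, and no patient-level covariate is named.

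The section on why randomisation is not used commits to a fixed centre effect with no condition attached. It also says that "patient cancer stage and tumor characteristics should be comparable (see inclusion criteria", and that a questionnaire before inclusion records whether a specific criterion drove the treatment choice.

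**The concern.** Without randomisation, the arms have no reason to be alike in expectation. Stage and preference are stated reasons for the choice, and stage and baseline swallowing may plausibly bear on swallowing at 12 months. The need for adjustment therefore follows from the design and not from what the baseline table shows.

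The stated rule makes adjustment depend on detecting an imbalance. A non-significant test in arms of 36 does not show that the arms are comparable; it often means only that the test could not see the difference. When a real imbalance goes undetected, the MDADI comparison proceeds with no patient-level adjustment, in exactly the trials that would describe their arms as comparable. The method of the primary comparison also depends on a look at the data against an unstated criterion.

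At stake are bias in the 12-month MDADI difference and a type I error above its nominal level.

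**Working it through.** **Inputs from the protocol.** SD 12 points (the score is assumed "normally distributed with a standard deviation of 12 points"), target difference 10 points, 95% confidence, 90% power, 30 patients per arm before dropout and 36 recruited.

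**Assumptions not in the protocol.** One measured prognostic baseline variable; one arm shifted by s SD on it (s = 0.3 to 0.5); correlation ρ = 0.5 to 0.6 with 12-month MDADI; no true treatment effect; a mismatch means a three-group Tukey test with p < 0.05; 36 patients per arm analysed.

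**Step 1: the plan's own sample size.** For one two-sided pairwise comparison, n = 2(1.960 + 1.282)² × 12² / 10² = 30.3, so 31 per arm against 30 stated. Power at 30 is 0.898. The stated figure is reproduced to within one patient; it contains no allowance for confounding adjustment.

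**Step 2: how often the baseline tests find a real imbalance (36 per arm).**

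| Imbalance in one arm | Tukey flags any pair | Missed |
|---|---|---|
| 0.3 SD | about 23% | about 77% |
| 0.4 SD | about 39% | about 61% |
| 0.5 SD | about 57% | about 43% |

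Any of the three pairs counts as a flag, because the trigger refers to the three groups. For a categorical factor, such as a cN1 share of 40% against 20% in each of the other two arms, the chi-square test flags it about 49% of the time.

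**Step 3: bias if nothing is adjusted.** Bias = 12 × ρ × s. The range runs from 12 × 0.5 × 0.3 = 1.8 points to 12 × 0.6 × 0.5 = 3.6 points. This is a reference value only, since never adjusting is not the plan.

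**Step 4: the plan's rule against always adjusting.** Each simulated trial is adjusted for the variable only if the Tukey test flags it. A pairwise contrast involving the shifted arm is then tested at 5%.

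| Quantity | Conditional rule | Always adjust for the same variable |
|---|---|---|
| Average bias | about 1 point (0.9 to 1.3) | about 0 |
| Bias in trials where the imbalance is missed | about 1.4 to 2.4 points | not applicable |
| Type I error | about 6% to 7% | about 5% |

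Against the 10-point target, the bias is about 10% on average and 14% to 24% in the trials where the imbalance is missed.

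**Step 5: what the centre effect covers.** It removes differences between centres, which is relevant because local expertise drives part of the choice. Centres must, however, have expertise in at least two modalities, so choice within a centre by stage, preference or baseline swallowing is to be expected. A centre term does not touch that.

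**The case against.** The strongest reply is that the plan does adjust when it sees a problem, and that the single-variable calculation understates how often it would. If any of eight independent baseline variables can trigger the analysis and all are then adjusted (both the count and the independence are assumed), one variable shifted by 0.4 to 0.5 SD leads to adjustment in 56% to 70% of trials. The residual bias is then about 0.7 to 0.8 points and the type I error 6.0% to 6.4%. With three variables shifted by 0.4 SD (correlation 0.35 each), adjustment is triggered in 82% of trials, with about 0.7 points of residual bias and a type I error of 8%. This stands: the bias is smaller than in the single-variable case, though not zero, and the error inflation remains.

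It is also fair to say that covariate lists and balance measures belong in a statistical analysis plan that is not shown. The condition itself, however, is written in this protocol.

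Four stronger readings are tempting, and the protocol does not support them:

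- *The primary comparison could be wholly unadjusted.* The fixed centre effect is promised in every case. What is not guaranteed is patient-level adjustment.
- *The Charlson index is the gatekeeper for adjustment.* The Tukey and chi-square tests cover demographics and tumour measures, and the trigger refers to baseline variables generally. Charlson is a weak stand-alone check, since comorbidity says nothing of stage or swallowing, but it is one check among several.
- *The expectation of comparable tumours contradicts allocation by stage.* That remark points to the narrow eligibility range, and the same sentence goes on to acknowledge preference and expertise. This is a tension, not a contradiction.
- *The bias is 1.8 to 3.6 points overall.* Those values describe never adjusting, which is not what the plan does.

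**Conclusion.** The point holds in limited form. The protocol makes patient-level confounding adjustment conditional where the design calls for it in every case, and the baseline tests that appear to supply the condition miss imbalances of 0.3 to 0.5 SD in about 43% to 77% of trials.

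The consequence is a moderate risk, not a demonstrated large bias. The figures rest on one measured confounder, a correlation of 0.5 to 0.6, and a mismatch read as p < 0.05; none of these is in the protocol. Several undetected confounders acting in the same direction would add up. A different threshold for mismatch would change the figures but would still leave the primary method dependent on a judgement made after seeing the data.

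**What to change.** Delete the condition on a discovered mismatch. Make a prespecified adjusted comparison of 12-month MDADI primary in all cases. Two suitable forms are:

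- the planned mixed model with centre plus a short list of baseline covariates: baseline MDADI, cT, cN, age, ECOG and Charlson;
- a three-group propensity score built on the same list.

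Describe baseline balance by standardised differences instead of significance tests. Keep Charlson as one covariate and drop its role as a separate check of heterogeneity. Report the result without patient-level adjustment as supportive.

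The cost is a change of wording, slightly more analysis, and some loss of precision or effective sample size. The covariates are routine baseline items already planned, so no new data collection should be needed. With roughly 30 completers per arm (36 × 0.8 = 28.8), the covariate set should stay small. Adjustment deals only with what is measured; unmeasured confounding remains and should be acknowledged as a limitation.

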### Inclusion criteria

Diagnosis of SSCC (with histological confirmation)cT1-T2 / cN0-N1/ M0 according to 8.^th^ TNM classification (UICC/AJCC) [36]WITH a MTB decision according to the NCCN or European guidelines [31, 32]Diagnostic imaging (Head and neck and pulmonary CT or PET/CT, ± IRM if needed) realized within 1 month before the study inclusion ≥ 18 years old and able to provide an informed consentECOG/WHO performance status ≤ 2 [37]

All participants must have a writing informed consent before their involvement.

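### The only test named for survival differences between non-randomised arms is a log-rank test without strata, weights or covariates; adjustment for stage is at most conditional and is not tied to the survival comparison

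*Protocol article*

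**What the plan says.** All places are in the protocol article.

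- **Allocation.** Under Methods – design, the local tumour board decides on treatment, and the criteria listed are clinical stage (cTNM), what the patient prefers, and local practice under international guidelines. The Inclusion criteria admit cT1-T2 and cN0-N1, so stage varies within the trial.
- **Survival comparison.** Under Statistical analysis, survival is estimated from the tumour board date to a two-year cut-off, "using the Kaplan–Meier method with differences compared using the log-rank test".
- **Cox model.** The next sentence reads: "A Cox multivariate regression analysis will be used to determine baseline factors predictive of survival". Treatment arm is not named as a term.
- **Propensity score.** Earlier in the same section, if the baseline variables are found not to match across the three groups, "a multivariate propensity scores analysis (PSA) will be undertaken to establish conditional randomness and comparability". No threshold for a mismatch is given and no outcome is named.
- **Centre.** Under Why not using randomization?, "a fixed center effect will be integrated in the statistical analysis". Again no outcome or model is named.

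**The concern.** The arms are formed partly on a prognostic factor, and the test named for comparing them on survival does not account for it. A log-rank test without strata or weights holds neither stage nor centre. The Cox model, which could hold both, is directed at a different question. What remains is a propensity score step that depends on a mismatch being noticed and that no sentence connects to survival.

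Oncological outcome is one of the four classes on which efficacy is to be compared. The Modelling analysis section also carries OS and DFS from this trial into a lifetime cost-effectiveness model. A difference due to case mix, or a real one hidden by case mix, could pass into both.

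**Working it through.** **The plan's own figures.** No number of deaths and no power is stated for survival. The only sized analysis is MDADI: 2 × (1.96 + 1.2816)² × 12² / 10² = 30.26, so 31 per arm against the stated 30. That reproduces, but it has no bearing on this point.

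**Expected deaths.** The Background gives two-year OS of 83% for TLM and 89% for TORS. For radiotherapy I assume 70% to 83%. With 36 per arm:
- radiotherapy at 83%: 36 × (0.17 + 0.17 + 0.11) = 16.2 deaths
- radiotherapy at 70%: 36 × (0.30 + 0.17 + 0.11) = 20.9 deaths

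**Effect of stage mix alone, with no treatment effect.** The documents give neither the cN1 share by arm nor a hazard ratio for cN1, so both are assumed. Two-year OS in the surgical arms is set at 86%, midway between 83% and 89%. Let p0 be the cN1 share in the surgical arms, p1 the share in Arm 1, and h the two-year cumulative hazard in cN0.

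1. Solve (1 − p0)·exp(−h) + p0·exp(−HR·h) = 0.86 for h.
2. Arm 1 survival is (1 − p1)·exp(−h) + p1·exp(−HR·h).

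Example with HR 2.5, p0 = 20%, p1 = 50%: h = 0.1179, so survival is 0.8888 in cN0 and 0.7448 in cN1. Check: 0.8 × 0.8888 + 0.2 × 0.7448 = 0.860. Arm 1: 0.5 × 0.8888 + 0.5 × 0.7448 = 0.8168, a drop of 4.3 points.

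Drop in Arm 1 two-year OS, in points:

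| cN1 hazard ratio | 50% v 20% | 40% v 20% | 50% v 30% |
|---|---|---|---|
| 2 | 3.1 | 2.1 | 2.0 |
| 2.5 | 4.3 | 2.9 | 2.6 |
| 3 | 5.3 | 3.5 | 3.2 |

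**Effect on the test.** Three-arm log-rank test, 36 per arm, two-year cut-off, no treatment effect, 3,000 simulated trials per scenario in the table: rejection at the nominal 5% level in about 5-9% of trials. Stratified by cN, it is about 5% throughout. Splits outside this range do more harm. In a separate set of 2,000 trials per scenario, with cN1 shares of 70/10/10%, hazard ratio 3 and cN0 survival of 75%, the unstratified test rejects in 44%.

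**Would the conditional rule catch the imbalance?** The tools named just before it are Tukey and chi-square tests. If mismatch means p < 0.05 (an assumption), a simulated chi-square test on cN with 36 per arm flags a true 40/20/20% split in 49% of trials and a 50/30/30% split in 43%.

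**The case against.** The strongest reply is that the survival comparison is not barred from adjustment. The propensity score rule stands just before the survival sentence, names no outcome, and could reach survival by weighting, matching or stratification. The centre effect is promised just as generally, and a centre-stratified log-rank test or a Cox term would meet it. Nothing excludes treatment arm from the Cox model. A condensed article may also leave strata and covariate lists to the full protocol or the SAP. All of this stands. A reader might infer that survival will be compared unadjusted by rule; the documents do not support that.

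A reader might also infer that stage decides the arm. Patient preference and local standard of care count too, the choice between TLM and TORS depends on local expertise, and both N stages are provided for under radiotherapy and under surgery. The section on randomization expects stage to be comparable. No sentence sends cN1 patients to Arm 1, so the assumed shares are illustrations.

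The size is limited as well. With 36 against 72 patients, the standard error of the survival difference is √[S1(1 − S1)/36 + 0.86 × 0.14/72], or 7.3 to 7.7 points across the table. Every drop in the table is smaller than that.

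The reply does not dispose of the point. The article does more than stay silent: it names a test and gives the Cox model a role, and neither choice fits the stated allocation. Adjustment that waits for a detected mismatch can be missed about half the time for splits such as 40/20/20%. Even once triggered, nothing says that it alters the log-rank test.

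**Conclusion.** The point holds in limited form. The named survival test takes no account of stage, although stage is one stated basis of treatment choice. Adjustment is conditional on an undefined mismatch, and neither the propensity score nor the centre effect is linked to survival.

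Under the assumed cN1 shares and hazard ratios, the distortion is 2.0 to 5.3 points in two-year OS and a type I error of about 5-9%. The upper end is close to the 6-point gap between the cited TLM and TORS figures (89% − 83%). That gives a sense of scale only, since it is a different contrast. The 44% error rate needs an imbalance outside the assumed range and should not be quoted as the expected effect. Survival is secondary and unpowered, so this is a worthwhile correction and not a threat to the primary analysis.

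**What to change.** - Make the arm comparison for OS and DFS adjusted whether or not a mismatch is detected. Options are a log-rank test stratified by cN (0/1), a Cox model with arm as the term of interest stratified by cN, or a comparison weighted by the protocol's own propensity score. Stratifying by cN removes confounding by cN only; weighting can also cover T stage and comorbidity.
- Keep the model sparse. About 16 to 21 deaths will not support many covariates.
- Report arm hazard ratios with 95% confidence intervals, and keep the crude Kaplan–Meier curves as description.
- State how the promised centre effect enters the survival comparison. The number of centres is not given, and few separate centre terms could be supported with so few deaths.

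The cost is a few sentences. Clinical N stage is already recorded for eligibility. The price is a small loss of precision.

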#### Oncological measures

Overall survival, Disease specific survival, Disease-free survival, loco-regional and distant cumulative recurrence rate (%). Time Frame: 24 months from the start of treatment.

Histopathological finding for surgical arms: section margins status (R0/R1 and distance in mm) and P16 or HPV tumor status.

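### Kaplan-Meier for disease-specific survival slightly overstates the 24-month probability of disease death; cumulative incidence should be reported for disease death and recurrence

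*Protocol article*

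**What the plan says.** Under Oncological measures, the protocol article lists "Overall survival, Disease specific survival, Disease-free survival, loco-regional and distant cumulative recurrence rate", all as secondary outcomes over 24 months.

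The Statistical analysis section gives one time-to-event method. Survival rates run to a cut-off at 2 years and use the "Kaplan–Meier method with differences compared using the log-rank test". A regression follows: "A Cox multivariate regression analysis will be used to determine baseline factors predictive of survival". The article does not say whether that model is cause-specific. It states no event definition for DSS, no rule for deaths from other causes and no competing-risk method. No method is attached to the recurrence rates.

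Two further statements bear on comparability between arms. Allocation is not randomised: "The treatment will be chosen by the local multidisciplinary tumor board (MTB"). On baseline differences the plan says: "Any difference in patient baseline heterogeneity between the arms will be assessed by the Charlson Comorbidity Index".

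**The concern.** DSS is a survival rate, so the Kaplan-Meier sentence covers it. In the usual DSS analysis, a patient who dies of another cause is censored at that death and is treated as though disease death could still follow. One minus the curve then estimates the risk of disease death in a setting where nobody can die of anything else. It is not the proportion of the arm that actually dies of disease, and it is always too high when other-cause deaths occur.

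Oncological outcome is one of the four outcome classes in the main objective, and readers will tend to take 24-month percentages as actual risks. The excess grows with other-cause mortality. In a non-randomised comparison it could therefore differ between arms for reasons unrelated to treatment.

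**Working it through.** The plan states no expected rate for DSS or recurrence in this trial, so it has no figure of its own to reproduce here. The only design figure used is 36 patients per arm, for the sampling error.

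**Inputs from the Background**
- 2-year overall survival (OS): 83% for TLM (pT1-T2) and 89% for TORS. No 2-year OS is quoted for radiotherapy.
- Regional control after radiotherapy: 70% at 5 years.

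**Assumptions (not in the documents)**
- Hazards are constant over the 2 years.
- The share *s* of deaths from other causes is 25, 50 or 75%.
- Other-cause death before recurrence is 5 to 20%.
- The 70% figure can be read as a net (Kaplan-Meier type) control rate.

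**Formulas.** Let H1 be the cumulative hazard of the event of interest at 2 years and H2 that of other-cause death.
- One minus Kaplan-Meier: 1 − exp(−H1)
- Cumulative incidence: H1/(H1+H2) × [1 − exp(−(H1+H2))]

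**Disease death.** H1+H2 = −ln(OS) and H1 = (1−s) × (−ln OS). The two quantities reduce to 1 − OS^(1−s) and (1−s)(1−OS).

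| OS | s | 1−KM | Cumulative incidence | Excess (points) |
|---|---|---|---|---|
| 83% | 25% | 13.04% | 12.75% | 0.3 |
| 83% | 50% | 8.90% | 8.50% | 0.4 |
| 83% | 75% | 4.55% | 4.25% | 0.3 |
| 89% | 25% | 8.37% | 8.25% | 0.1 |
| 89% | 50% | 5.66% | 5.50% | 0.2 |
| 89% | 75% | 2.87% | 2.75% | 0.1 |

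**Recurrence, only if Kaplan-Meier were used.** H1 = −ln(0.70) × 2/5 = 0.1427, so 1−KM at 2 years is 13.3%. With H2 = −ln(1 − other-cause death):

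| Other-cause death | Cumulative incidence | Excess (points) |
|---|---|---|
| 5% | 13.0% | 0.3 |
| 10% | 12.6% | 0.7 |
| 15% | 12.3% | 1.0 |
| 20% | 12.0% | 1.3 |

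A deliberately extreme case, 30% net recurrence with 20% other-cause death, gives 30.0% against 27.1%, an excess of 2.9 points.

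**Difference between arms.** Suppose two arms share the same net recurrence of 20% but have 5% and 15% other-cause death. The excesses are 0.5 and 1.5 points, so the bias differs by 1.0 point. Both other-cause rates are hypothetical.

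**Sampling error.** The binomial standard error, √[p(1−p)/36], is 5.0, 6.7 and 7.6 points at p = 10, 20 and 30%. At the lowest disease-death rate in the table (2.87%) it is √(0.0287 × 0.9713/36) = 2.8 points, against an excess of 0.1.

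**The case against.** The case against has several parts.

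- **The censoring rule is inferred.** The article never says that other-cause deaths are censored, and such rules may sit in the full protocol or an analysis plan that is not shown. This stands as a limit on certainty. It does not remove the point, because the article does fix the estimator for survival rates, and censoring is what that estimator conventionally does with DSS.
- **Kaplan-Meier DSS is a recognised quantity.** It estimates net survival and misleads only when its complement is read as the share dying of disease. That is correct, and it is why the remedy adds an estimate and does not remove one.
- **The log-rank test might seem invalid for DSS.** It is not. With other-cause deaths censored it compares cause-specific hazards, which is a legitimate question. Moving to Gray's test would change what is estimated; it would not correct an error.
- **A reader might infer that the recurrence percentages are biased as planned.** The documents do not support this. The Kaplan-Meier sentence concerns survival rates, and a cumulative recurrence rate could already mean cumulative incidence or a crude proportion.
- **A reader might infer that the plan expects comorbidity to differ, so that one arm is penalised.** The plan only undertakes to assess any difference with the Charlson index. It excludes serious comorbidity, provides a propensity score analysis if baseline variables are mismatched, and nowhere indicates which arm would be more comorbid. Differential bias is possible but not shown. Balancing comorbidity would still leave the overstatement within each arm.

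**Conclusion.** The point holds for DSS, at small size. The stated method gives a complement that overstates the actual 24-month probability of disease death by about 0.1 to 0.4 points at the Background's 2-year OS. This rests on constant hazards and an assumed split of deaths by cause. For recurrence the point is conditional on Kaplan-Meier being used: about 0.3 to 1.3 points for 5 to 20% other-cause death. The direction is certain whenever other-cause deaths are censored; the size depends on those assumptions.

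OS is unaffected, and so is disease-free survival if any death counts as an event. These are secondary endpoints, and the effect is well inside the sampling error, so it is unlikely to alter a conclusion. This is an inexpensive improvement to what is reported and does not threaten the trial's inference.

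**What to change.** - Keep Kaplan-Meier and log-rank for OS and disease-free survival.
- Keep log-rank or Cox for comparing arms on DSS, described as a comparison of cause-specific hazards with other-cause deaths censored.
- Report the 24-month probabilities of disease death, loco-regional recurrence and distant recurrence as Aalen-Johansen cumulative incidence, with death from other causes as a competing event.
- Show the cumulative incidence of other-cause death by arm beside them, so that any imbalance is visible.

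The cost is about one sentence of analysis text. No extra data are needed, because DSS already requires the cause of death. The sample size and the primary analysis do not change.

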### Primary outcome measure

Clinical Dysphagia QoL evaluation after treatment will be assessed using MD Anderson Dysphagia Index (MDADI) at 1 year [38, 39]. It contains 20 items; ranged in score from 0 to 100 (a high scale score represents a higher response level). Time Frame: baseline (before treatment), 3 – 6 – 9 – 12 – 18 – 24 months after treatment.

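### Free improvement: the plan compares raw 12-month MDADI between non-randomised arms and does not commit to adjusting for the baseline MDADI it collects

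*Protocol article*

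**What the plan says.** All references are to the protocol article.

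- **Endpoint** (Statistical analysis): "The primary outcome is the total MDADI scores at 12 months between the 3 arms". This is a score, not a change from baseline.
- **Schedule** (Primary outcome measure): "Time Frame: baseline (before treatment), 3 – 6 – 9 – 12 – 18 – 24 months after treatment". A pre-treatment MDADI is therefore available.
- **Model** (Statistical analysis): "The scores of the different scales will be compared between the 3 arms using mixed models for repeated measures". The article names no response vector, visit terms or covariates.
- **Allocation** (Methods – design): the local tumor board chooses treatment by stage, patient preference and local practice.
- **Eligibility** (Exclusion criteria): only dysphagia unrelated to the cancer or the biopsy is excluded.
- **Handling of baseline differences** (Statistical analysis; Why not using randomization?): demographics and imaging tumor measures are described. Differences are tested with Tukey or chi-square tests. Heterogeneity between arms is assessed by the Charlson Comorbidity Index. A propensity analysis follows only if a mismatch is discovered. A fixed center effect is included in any case.
- **Sample size** (Statistical analysis): "Assuming that the MDADI total score is normally distributed with a standard deviation of 12 points" and "considering a minimal clinical difference of 10 points", giving 30 evaluable and 36 recruited per arm.

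**The concern.** Pre-treatment swallowing is a plausible confounder here. It is likely to predict swallowing at 12 months, it can vary at entry because tumour-related dysphagia is admitted, and it may differ between arms because treatment is chosen rather than assigned. A raw 12-month comparison would then mix pre-treatment differences with the effect of treatment.

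The article does set out how baseline differences will be handled, but that strategy does not reliably reach this variable. The Charlson index does not measure swallowing. A center effect does not remove differences between patients within a center. The propensity step is conditional on a test in small arms, and its variables are not listed. A team could follow the text faithfully and leave a material swallowing difference in the primary contrast. Some precision would be lost as well, though in a non-randomised comparison confounding matters more.

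**Working it through.** **Inputs from the article:** SD 12, target difference 10, 95% confidence (two-sided 5% assumed), power 90%, 30 evaluable and 36 recruited per arm.

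**Assumptions, not in the article:** baseline-to-12-month correlation ρ of 0.4, 0.5 or 0.6; the SD of 12 also holds at baseline; a linear relation; a baseline difference of 0.5 SD, that is 6 points, between two arms.

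**1. The plan's own figure.** n = 2(1.960 + 1.282)² × 12²/10² = 30.3, so 31 per arm (32 with the t distribution). At 30 per arm the standard error of a pairwise contrast is 12√(2/30) = 3.10, and power is 89.8% by the normal formula and 88.8% by the t distribution. The article's 30 is reproduced within two patients. It rests on one unadjusted pairwise contrast and uses no baseline correlation.

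**2. Would the trigger work?** Suppose the Tukey test were applied to baseline MDADI in all 36 patients per arm. The standard error is 12√(2/36) = 2.83, so a 6-point difference gives a noncentrality of 6/2.83 = 2.12. The Tukey critical value for three groups and 105 degrees of freedom, on the t scale, is 2.38. The chance of detection is about 40%. An omnibus F test would give 45% to 57%, depending on where the third mean lies.

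**3. What an undetected difference leaves behind.** With equal SDs, the bias in the unadjusted 12-month contrast is ρ × 6.

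**4. Precision.** Adjusted SD = 12√(1 − ρ²). Power is for 10 points at 30 per arm, by the normal formula with balanced baselines.

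| ρ | Bias from 6-point imbalance | Adjusted SD | SE | Power |
|---|---|---|---|---|
| 0 (unadjusted) | – | 12.0 | 3.10 | 89.8% |
| 0.4 | 2.4 | 11.0 | 2.84 | 94.1% |
| 0.5 | 3.0 | 10.4 | 2.68 | 96.1% |
| 0.6 | 3.6 | 9.6 | 2.48 | 98.1% |

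Against the 10-point target, the bias is 24% to 36%.

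**5. The two gains are not fully additive.** If baseline differs by 6 points between the two arms, the variance of the adjusted contrast is about SD²(2/30 + 6²/(58 × 12²)) rather than SD² × 2/30. The bracket rises from 0.0667 to 0.0710, so the standard error grows by about 3%. At ρ = 0.5 it goes from 2.68 to 2.77, and power from 96.1% to 95.1%.

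**The case against.** The strongest reply is that silence is not a decision. The article is condensed, an analysis plan may exist, and a mixed model's covariate list is commonly left to it. That stands against any claim that the model omits baseline. A reader might infer such an omission, but the text neither includes nor excludes baseline MDADI. It does not dispose of the point, because the article does fix a strategy for baseline differences, and that strategy is conditional and does not name MDADI.

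Second, baseline is one of the scheduled MDADI assessments, so it may enter the model as a response. That is possible. However, with a separate mean for each arm at each visit, the 12-month arm contrast is still uncorrected for baseline. Correction needs a change contrast, a common baseline mean or a covariate, and the article states none of these.

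Third, the propensity analysis could include MDADI, and a pre-inclusion questionnaire records whether a specific criterion influenced the treatment choice. Both are real safeguards. The first depends on a check that would often miss a 6-point difference; the second records reasons and is not tied to any adjustment.

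Fourth, a reader might infer that the mixed model yields an arm effect averaged over 3 to 24 months. Nothing in the article proposes this, and both relevant sections fix the primary outcome at 12 months. It is also uncertain whether the mixed-model sentence governs the primary total score, since its paragraph opens with subscales and single items.

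Fifth, the size of the effect rests on assumed correlations and imbalance. That stands in full. Power figures that start from a Tukey-adjusted primary contrast after dropout would also go beyond the text, because the Tukey test is mentioned directly after the baseline descriptions. The working above therefore uses the plan's own single contrast for power.

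**Conclusion.** The point holds as a free improvement. The article does not commit the primary contrast to the baseline MDADI it collects, and its stated safeguards can leave a swallowing difference in place. Under the stated assumptions, a 6-point baseline difference would pass a Tukey check about 60% of the time and shift the 12-month contrast by 2.4 to 3.6 points. Adjustment would also lift power at 30 per arm from just under 90% to about 94 to 98% with balanced baselines, and slightly less otherwise.

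A reader might go on to infer that the sample size is wrong. It is not on this account: the calculation does not depend on baseline adjustment, and adjustment would only add margin. The true gain and bias cannot be fixed from the article, which gives neither a correlation nor an expected baseline difference.

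**What to change.** In Statistical analysis, state that the primary model is a mixed model on the post-treatment MDADI total scores (3 to 24 months) with arm, visit, arm-by-visit, baseline MDADI and baseline-by-visit. Baseline enters whatever imbalance is observed, alongside the fixed center effect and any propensity analysis. Name the arm contrast at the 12-month visit as the primary estimate. Treat the QLQ-C30 and H&N43 scales the same way, each with its own baseline.

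The cost is a sentence or two. The data are already scheduled, and neither recruitment nor the sample size changes. The text should not promise too much: baseline MDADI is measured with error, so adjusting for it reduces confounding without removing all of it, and confounding by other factors remains a matter for the propensity analysis.
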